#### Secondary outcomes

Secondary efficacy outcomes focus on the most relevant sequelae of ICU patients and encompass physical, mental and social impairments. The mental component summary score (MCS) of the SF-12 questionnaire will be the first of our measured secondary outcomes. Activities of Daily Living (ADL) will be assessed by the Barthel-Index [54, 55], which evaluates ten everyday functions. The degree of independence or care dependence can be assessed on a score ranging between 0 (complete need for care) and 100 points (independence). The Chair Rise Test [41, 56] and measurement of the hand grip strength will be used to assess participants‘ physical functioning and muscular strengths. In the Chair Rise Test, anyone who cannot get up from a chair at normal height five times in 11 s or less without supporting himself with his arms is considered to be at a higher risk of falling. The hand grip strength as an indicator of overall muscle strength will be assessed using a digital dynamometer (Jamar Plus+ Digital Hand Dynamometer) [42, 57]. We will measure the grip strength of both hands and use the maximum of these values for comparison with the standard values of Dodds et al. [58] stratified by age and sex expressed in percentiles, mean and standard deviation. The assessment of psychopathological symptoms comprises anxiety and panic disorder, depression and post-traumatic stress disorder (PTSD). PTSD is measured by the German translation: (Maercker, A. (1998) Posttraumatische Stress Skala-10 (PTSS-10) – deutsche Version modifiziert nach Schüffel u. Schade, unpublished manuscript, Universität Zürich, Klinische Psychologie II) of the Post-Traumatic Stress Syndrome 10-Questions Inventory (PTSS-10) [59], which consists of two parts. The first part assesses memories of traumatic experiences during the ICU stay (e.g. nightmares) and the second part measures the intensity of ten PTSD symptoms (e.g. emotional numbing) experienced presently by the participants. Each symptom is rated from one (never) to seven (always). A total score of more than 35 predicts a likely diagnosis of PTSD [60]. The other psychopathological symptoms will be measured by using modules from the German version of the Short Form of the Patient Health Questionnaire (PHQ-D) [61]. This brief screening instrument with 15 items is designed to establish DSM-IV (Diagnostic and Statistical Manual of Mental Disorders) [62] criteria-based psychiatric diagnoses. We will use the questions on depression and anxiety and panic disorders. The extent of ambulatory and stationary health care use among the former ICU patients will be assessed by self-reported contacts with health services using a questionnaire. In addition, HRQOL of next of kin will be assessed using the SF-12 questionnaire (MCS and PCS).

### Outcome assessment

Outcomes will be assessed at 6 months after discharge from ICU. Study participants will be asked to visit the study centre for outcome assessment. Trained study personnel will hand out self-report questionnaires, provide standardised instructions and perform physical measurements. Missing data will be minimised by having study personnel available at all times to check the completeness of the questionnaires or to answer participants´ questions. If participants cannot visit the study centre, home visits will be scheduled. If a participant discontinues the trial before outcome assessment, only the baseline data and the reasons for discontinuation are included in the analysis.

### Data analysis

A Data use and Access Committee, consisting of the three consortium partners, is part of our study, which will monitor the entire planned use of the data and releases it for analysis (see Fig. 6). We will write a statistical analysis plan before doing any data analysis. Group allocation will be masked by our trust centre during analysis of the primary outcome. The treatment effect (ICU follow-up clinic) on HRQOL as primary outcome and the secondary outcomes will be assessed using analysis of covariance according to the intention-to-treat-principle. Thus, all randomly assigned participants will be included in a complete case analysis. Multiple imputation will be considered for missing follow-up data as part of sensitivity analysis [63]. Descriptive statistics will be used to determine participant characteristics and to check their distribution at baseline in the intervention and control group. For sensitivity analysis, a per-protocol analysis will be performed additionally. The primary outcome physical HRQOL will be compared 6 months post randomisation. We will calculate point and interval estimates with the respective confidence intervals for the difference in medians. Secondary analysis will be performed depending on scale level and for descriptive purposes only. No formal hypothesis testing will be performed.

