### Sample size

We chose a total of 100 participants for the pilot study, i.e. 50 per arm. This sample size is expected in literature to allow for a detailed analysis of feasibility and to be sufficient for an estimation of the difference in HRQOL (continuous variable) between intervention and control group which will be used for sample size estimation for the future pragmatic trial [32, 33].

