### Potential efficacy outcomes

#### Primary outcome

Primary efficacy outcome will be the physical health-related quality of life at 6 months after informed consent/ICU discharge. We chose this outcome as primary outcome because physical impairments are very common at 6 months. For example, a study from the UK reported mobility problems 6 months after the ICU stay in 64% of ICU survivors [46]. A prospective multi-centre study in Germany also showed that the limitation of the physical component is more pronounced at 6 months compared to the mental component [47]. Physical health-related quality of life will be assessed by the physical component scale (PCS) of the Short Form-12 self-report questionnaire (SF-12) [48]. This comprehensive, generic questionnaire comprises overall twelve items resulting in a physical (PCS) and mental component scale (MCS, see secondary outcomes), which will be scored according to published algorithms (German norm values; resulting in a standard score with mean = 50 and standard deviation = 10) [49]. Scores can range between 0 and 100, with higher values indicating higher HRQOL. The questionnaire has been used in critically ill patients before [23, 50], takes only minutes to complete and can be self-completed or interviewer assessed. Psychometric properties have not been tested in former critically ill patients so far, but studies on validity and reliability of the SF-12 in populations of older patients, which also applies to most former intensive care patients, show acceptable measurement characteristics [51, 52]. In our study we will use the German translation with a 1-week recall period [53].

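### The primary efficacy outcome is assigned to ANCOVA but its estimate and interval are promised for a difference in medians, which ANCOVA does not give, so the primary estimate is not uniquely fixed

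*Protocol article*

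**What the plan says.** All references are to the protocol article.

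- **Data analysis, model.** The treatment effect on HRQOL as primary outcome, and on the secondary outcomes, "will be assessed using analysis of covariance according to the intention-to-treat-principle". No covariates are named.
- **Data analysis, effect measure.** Further down the same paragraph: "The primary outcome physical HRQOL will be compared 6 months post randomisation". The next sentence reads: "We will calculate point and interval estimates with the respective confidence intervals for the difference in medians". It does not say how the median difference is estimated, or whether it is adjusted.
- **Data analysis, inference.** "No formal hypothesis testing will be performed".
- **Sample size.** The planned number is described as "sufficient for an estimation of the difference in HRQOL (continuous variable) between intervention and control group", and that estimate is to be used in sizing the future trial. The last paragraph of the Background and the Trial design section state the same planning purpose.
- **Primary outcome.** PCS is scored on German norms, "resulting in a standard score with mean = 50 and standard deviation = 10".

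**The concern.** The plan names a model and an effect measure for the same outcome, and the two do not match. This is not detail deferred to the statistical analysis plan: a later plan could honour both sentences only by adding a method that the protocol does not mention, or by dropping one of the two.

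Because there is no hypothesis testing, the point estimate and its interval are the whole efficacy result. They are also a stated input to the design of the next trial. A standard formula for a continuous outcome needs a mean difference and an SD, and a difference in medians supplies neither directly. With few patients per arm, the two estimates can also differ noticeably in the same data, so it matters which one is named in advance.

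**Working it through.** **1. Is there a figure to reproduce?** No. The sample size is given without a target difference, SD, error rate or power, so the check is on what each method estimates and how precisely.

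**2. What each sentence yields.** ANCOVA gives an adjusted difference in means, its interval and a residual SD. A difference in medians needs another method, such as raw sample medians, quantile regression or a Hodges-Lehmann shift. None is named.

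**3. Inputs for precision.**
- SD = 10. This is the norm-population scaling in the Primary outcome section. No SD for ICU survivors is given, so its use here is an assumption.
- n = 50 per arm as first planned ("We chose a total of 100 participants for the pilot study, i.e. 50 per arm"), and n = 20 per arm after the cut to 40 participants in the Amendment to protocol section, assuming equal allocation.
- r = correlation between the ANCOVA covariates and PCS at 6 months, taken as 0 to 0.5 (assumption).

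**4. Formulas.**
- Mean difference: SE = SD × √(2/n).
- ANCOVA: SE = SD × √(2/n) × √(1 − r²).
- Raw median difference, normal data, large-sample: SE = SD × √(2/n) × √(π/2).
- 95% half-width = 1.96 × SE.

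**5. Results for normal data.**

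| | 50 per arm | 20 per arm |
|---|---|---|
| Mean difference, SE | 10 × √(2/50) = 2.00 | 10 × √(2/20) = 3.16 |
| Half-width, ANCOVA r = 0 | 3.92 | 6.20 |
| Half-width, ANCOVA r = 0.3 | 3.74 | 5.91 |
| Half-width, ANCOVA r = 0.5 | 3.39 | 5.37 |
| Raw median difference, SE (large-sample) | 2.51 | 3.96 |
| Raw median difference, half-width (large-sample) | 4.91 | 7.77 |
| Raw median difference, SE (100,000 simulated trials) | 2.47 | 3.83 |
| Hodges-Lehmann shift, SE (5,000 simulated trials) | 2.05 | 3.32 |

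At 20 per arm the simulated ratio is 3.83/3.16 = 1.21, and at 50 per arm 2.47/2.00 = 1.24. The Hodges-Lehmann shift costs only 2.05/2.00 and 3.32/3.16, that is about 2% and 5%.

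**6. Dependence on the distribution.** Simulated ratio of the SE of the raw median difference to that of the mean difference, all data scaled to SD 10:

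| Distribution | 50 per arm | 20 per arm |
|---|---|---|
| Normal | 1.24 | 1.21 |
| t with 5 df | 1.01 | 1.00 |
| Lognormal skew | 1.03 | 1.02 |
| Laplace | 0.78 | 0.82 |

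**7. How far the two estimates part.** With normal data, SD 10 and 20 per arm, the raw mean and median differences lie more than 2 points apart in about 35% of simulated trials. They have opposite signs in about 13 to 14% at a true effect of 3 points and about 7% at 5 points. Both effect sizes are assumptions.

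**The case against.** Several stronger readings are tempting, and the document does not support them.

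- **That the median difference is unadjusted.** This is a natural inference, but the text does not say so. Quantile regression is not ruled out.
- **That it is the less precise estimate.** This holds for raw medians of near-normal data. Step 6 shows the loss vanishing or reversing elsewhere, and the document gives no PCS distribution for this population. A statement that about a third of the patients are wasted would rest on the normal case alone.
- **That adjustment gains are thrown away.** No covariate is named, and the document disagrees with itself on whether physical HRQOL is measured at baseline: Participant characteristics limits baseline HRQOL to the EQ-5D VAS, while Data collection, management and privacy issues has participants report physical HRQOL at baseline. The gain is unknown.
- **That the median difference is the headline result.** The sentence directly follows the one on comparing the primary outcome, but neither estimate is ranked.
- **That planning is blocked.** ANCOVA would supply a mean difference and residual SD, and nothing forbids reporting them.

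The other side can add that feasibility is the primary objective, that the Discussion concedes the sample is too small for a full effectiveness evaluation, and that an analysis plan written before analysis, with masked group allocation, limits choosing between estimates after seeing results. Both can also be computed from the same data, so nothing is lost for good. All of this stands and lowers the severity. None of it makes the named model yield the named effect measure.

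**Conclusion.** Wrong as written; moderate severity. The paragraph pairs ANCOVA with an effect measure that it does not estimate, names no linking method and ranks neither estimate, so the primary efficacy estimate is open. That conclusion needs no assumption.

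The precision cost does need assumptions. It is about 21% in standard error at 20 per arm if raw medians are meant and PCS is near normal with SD 10. It is about nil or reversed under the other distributions tried, and small for a Hodges-Lehmann shift. It should not be quoted without those conditions. No error rate is affected, and efficacy is exploratory here, so the practical consequence is an ambiguous estimate that may not be in the form needed to size the next trial.

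**What to change.** Replace the medians sentence in the Data analysis section with: *The primary efficacy estimate is the ANCOVA-adjusted mean difference in SF-12 PCS at 6 months with its 95% CI; the residual SD will be reported for planning, and group medians and quartiles are given descriptively.* If skew is feared, use a bootstrap or robust interval for the same mean difference.

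If the investigators do want medians as the main measure, the contradiction can also be removed by replacing ANCOVA with a named method that estimates them, and reporting means and SDs for planning.

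Either way the cost is one sentence in the protocol, carried into the analysis plan, with no extra data and no burden on patients.

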**Fig. 6 Fig6:**
[figure not shown]
Flow of study data in the PINA project

### Ethical principles and description of risks

The institutional Ethics Committee of the University of Regensburg (19-1522-101) approved the study protocol. The study is planned and conducted in accordance with the declaration of Helsinki, the medical professional codex, the European General Data Protection Regulation (DS-GVO) and the Federal Data Protection Act (BDSG). Participants (and next of kin) will participate voluntarily and will give written informed consent. Participants will be informed that they can cancel their participation at any time without disclosing reasons for their cancellation and without negative consequences for their future medical care. This also applies to participants in the intervention group who already made use of ICU follow-up services.

The risks for participants arising from participation in the study are generally considered low. No negative effects of ICU follow-up clinics are reported [24]. Therefore, there are no specific risks related to the intervention and thus no rules for stopping the intervention.

### Data collection, management and privacy issues

For study purposes, quantitative and qualitative primary data as well as clinical data will be collected. In order to keep the burden on the participants as low as possible, as much data as possible will be extracted directly from the hospital records (contact information, disease- and therapy-related characteristics, sociodemographic characteristics). More detailed information on sociodemographic characteristics will be obtained directly from the participants. Participants themselves will provide information on the primary outcome physical HRQOL at baseline and follow-up. At follow-up, further patient-reported outcomes are recorded as well as self-reported health care utilisation and physical functioning (e.g. Chair Rise Test). HRQOL of next of kin will also be recorded at follow-up. Personal information will only be collected on the consent form. These will be stored in the Trust Centre in locked cabinets without access by unauthorised persons.

All data will be handled according to the Medical Confidentiality Rules and German Federal Data Protection Act (BDSG), as well as the European General Data Protection Regulation (GDPR/DS-GVO) and all subordinate acts and ordinances. Except for contact information required for phone monitoring and home visits, all data will be recorded and stored pseudonymously. Person-identifying data will be handled by a trust centre and stored separately from study data and can only be linked via a separately stored pivot table on a PC without access to the internet. The chances that an illicit link can be made between the data are very small in light of the precautions we have taken. Therefore, the risk of an unauthorised de-pseudonymisation of the study participant’s data is considered extremely low (see recital 75 DS-GVO). In this context, we have drawn up a comprehensive data protection concept. All study related data and documents will be stored on protected servers of either the University of Regensburg or the University of Magdeburg. Only members of the study team will have access to the respective study files. Data exchange between the study team and the outcomes assessor will be via a secure platform where study data can only be accessed via double authentication (username/password for login and additional password to access the database). We have summarised the data flow schematically in Fig. 6.

### Amendment to protocol

Due to the COVID-19 pandemic, the Bavarian authorities ordered restrictions on research activities at all study centres. Therefore, all activities related to recruitment, inclusion of participants, the work of the follow-up clinic as well as the follow-up survey had to be discontinued on 20 March 2020. As a result, we needed to plan for a restart of the RCT. Since the duration of the interruption was not foreseeable at this time, there was initially no other choice than to completely restart this pilot RCT afterwards. In a RCT, differences between the intervention group and the control group should be determined. However, if a part of all patients were treated before the pandemic and another part of the patients were treated during or even after the pandemic, these patients cannot be compared with each other anymore, as the care provided and the circumstances repeatedly changed. Furthermore, it was not foreseeable whether and how the intervention (ICU follow-up clinic) could have been carried out. After intensive consultations among the study team, with the hospital management and the funding body, it was decided to reduce the number of cases to 40 participants. This measure had to be taken mainly for research economic reasons. The limited duration of the project and limited financial resources did not allow a further extension of the project to recruit another 100 patients. We were able to resume activities on 15 June 2020 and believe that even with this reduced number of study participants, our overall aim to evaluate feasibility and effects of an ICU follow-up clinic can still be achieved. Study completion is expected in May 2021.

## Discussion

To our knowledge, PINA is the first study evaluating the feasibility and preliminary effects of a complex intervention in form of an ICU follow-up clinic for ICU survivors in Germany. Based on the key elements of development and evaluation of complex interventions using the framework of the medical research council (MRC) [29], this study concerns mainly the phases *development*, *feasibility and piloting*.

We have invested significant resources in the *development* of the intervention which was done by a participatory process in which patients, next of kin and health care professionals were involved. To be more precise, focus groups with health care professionals and one-to-one interviews with experts from the PICS field were conducted. At the same time, face-to-face interviews with patients and with next of kin were conducted. The results of these qualitative research projects were then further elaborated into a final concept in several workshops.

The implementation of the complex intervention in the *feasibility and piloting phase* aims at testing procedures, estimating retention and determining the sample size. In spite of the sample size being too small for a full effectiveness evaluation, we will determine effectiveness preliminarily, thus anticipating the full-scale *evaluation phase* in a large pragmatic trial in the future. The implementation will be monitored by process evaluation to provide insights into unexpected or unanticipated consequences or to show why the intervention works. Depending on the evaluation and feasibility outcomes, the next steps will be either to modify the intervention and repeat the piloting phase or to proceed to implement the intervention on a large scale and test it in a pragmatic real-world RCT.

### Limitations

Even though the randomisation process may have been conducted correctly using appropriate randomisation strategies, a balanced distribution of known and unknown confounding factors (such as sociodemographic or clinical factors) between intervention and control group might not be achieved. Therefore, we will compare baseline characteristics of participants in the intervention and the control group. The follow-up period may be too short, and the effects of the intervention might appear only after the follow-up period of 6 months. A minimal spillover effect, e.g. due to the information about the study, cannot be completely ruled out.

### Strengths

The study introduces the first ICU follow-up clinic in Germany and thus tries to improve the aftercare of ICU survivors. The greatest advantage of the ICU follow-up clinic is its participatory development, which increases the likelihood of the intervention being effective. In addition, all intervention treatments will use the standard health care system processes, allowing the ICU follow-up clinic to be well integrated into the existing health care system in the future.

### Trial status and dissemination

The first participant was enrolled on 2 December 2019. Participants’ recruitment started at the time of submission of the study protocol and was completed during the review process. Results will be presented at national and international conferences and reported in peer-reviewed journals.

## Data Availability

Data can be requested from 1 year after study completion from the principal investigator.
